## Abstract

**Background:**

Morbid obesity is a complex chronic condition characterized by a body mass index of 40 kg/m^2^ or higher. The incidence of the condition is on the rise in developed countries, and bariatric surgery has been proposed as a potential solution to address this trend. Nonetheless, bariatric surgery may also result in adverse effects, including a reduction in bone mineral density (BMD) and muscle mass, as well as an increased risk of fractures. The present study aims to elucidate the effects of bariatric surgery and whole-body vibration (WBV) training on body composition, microbiota, physical fitness, quality of life, and cardiometabolic markers.

**Methods:**

Twenty-eight participants (14 females), aged 18 to 50 years, will undergo sleeve gastrectomy surgery. They will be randomly allocated into a control group or a WBV training group. The WBV group will train three times per week with increasing intensities and duration ranging from 30 to 45 min over the 4-month training period. Measurements of body composition (dual-energy X-ray absorptiometry and peripheral quantitative computed tomography), physical fitness (muscular strength, agility, cardiorespiratory fitness, and balance), gait biomechanics, cardiometabolic markers, gut microbiota, quality of life, and physical activity levels will be collected at four different time points: (1) prior to the surgery, (2) 45 days post-surgery, (3) 6 months post-surgery, and (4) 18 months post-surgery.

**Discussion:**

Both groups are expected to experience improvements in most of the aforementioned variables. Nonetheless, we expect the WBV group to show larger improvements proving that the training is effective and safe.

**Trial registration:**

Clinicaltrials.gov NCT05695599. Registered on January 25, 2023.

**Supplementary Information:**

The online version contains supplementary material available at 10.1186/s13063-024-08221-7.

## Introduction

### Background and rationale

Obesity is a multifactorial disease with a prevalence that has tripled since 1980 [1]. By 2025, obesity is projected to increase in 44 European countries, with a described prevalence of obesity of 20% or more in 33 of the 53 European countries [2]. Moreover, the rates of morbid obesity are predicted to increase to 8% and 11% in developed countries such as England and Wales, respectively, by 2035 [3].

The World Health Organization defines morbid obesity as a complex chronic condition characterized by a body mass index (BMI) of 40 kg/m^2^ or higher. It has a significant impact on health, increasing the risk of several comorbidities, affecting the ability to work, and reducing life expectancy by up to 10 years [4]. Consequently, it results in a considerable economic burden on both the individual and society at large. In fact, it has been estimated that European Union countries spend around 7% of their healthcare budgets on treating obesity-related diseases [5, 6].

Although lifestyle changes based on nutrition and physical activity can improve the management of people with obesity, for patients with morbid obesity, surgical treatment through bariatric surgery (BS) has been demonstrated to be more effective and cost-effective than non-surgical measures [7]. BS modifies the composition and functionality of the gut microbiota, thereby reducing the dysbiosis associated with severe obesity and contributing to the remission of obesity-associated comorbidities [8, 9]. The intervention exerts a profound influence on appetite and glucose homeostasis, with gut-derived hormones and the intricate interplay between microbiota, intestine, liver, immune system, and brain playing a pivotal role [10, 11]. The changes in microbiota that occur following BS appear to be approach-specific and overlap with those related to alterations in food habits [12]. While BS is associated with a number of beneficial effects, some types of BS can lead to the malabsorption of calcium and vitamin D, potentially causing adipokine disorders, decrease in bone mineral density (BMD) [13], and an increased risk of fracture in the future [14].

A recent meta-analysis comprising 22 studies evaluating BS patients found that the decrease in BMD was larger in the femoral neck than in the lumbar spine [15]. Additionally, a time-dependent loss of BMD was observed, with larger decreases found in longer follow-up periods. This is consistent with another recent meta-analysis that included 14 studies which evaluated volumetric BMD and bone quality finding negative effects of Roux-en-Y gastric bypass on these variables [16]. The growing evidence of the adverse effects of BS on bone is clear, with the European Calcified Tissue Society publishing a position statement in 2022 stating that BS is associated with a 21–44% higher risk of all fractures [17].

The reduction in BMD may be attributed to a number of factors, including mechanical unloading resulting from a loss of body mass, loss of muscle mass, impaired calcium absorption, changes in hormonal status, and increases in bone marrow adiposity [17]. These factors may also increase the risk of fractures due to alterations in the center of mass, walking biomechanics, and a reduction in muscle mass and strength of the lower limbs. A recent meta-analysis demonstrated that post-surgery exercise interventions can have a positive effect on BMD [18]. In addition, exercise has been shown to have beneficial effects on gut microbiota composition and diversity [19–21] and in reducing inflammation [21, 22]. However, the meta-analysis only included three studies that combined resistance and aerobic training in two to five weekly sessions with an average duration of 45 min per session. Although these interventions are interesting, they require a significant amount of material and space, which makes them difficult to develop. Consequently, shorter and simpler interventions that can be performed in medical clinics and hospitals are needed to maintain participant motivation and avoid the need for a lot of space and equipment.

Whole-body vibration (WBV) training may be a potential solution, as this type of training has demonstrated to be effective in improving body composition and strength in obese patients [23, 24]. Research from our group has shown that it can also improve balance [25] and bone mass [26] in populations with compromised bone mass. In addition, the vibrating platform is only about 1 m^2^, so training can take place in a small space. Therefore, it could be an ideal method for clinics and hospitals to implement.

### Objectives

The objective of the present project is to describe the impact of vertical sleeve gastrectomy (SG) on a range of variables, including body composition (bone, fat, and lean mass), inflammatory, cardiometabolic, liver and bone biomarkers, fecal microbiota, balance and postural control, walking biomechanics, anxiety and depression, levels of physical activity and physical fitness, and quality of life. Furthermore, the study will assess the impact of a 4-month WBV intervention on the aforementioned variables. Finally, the results will enable us to assess the cost-effectiveness of the intervention.

## Material and methods

### Study design, research ethics approval, protocol registration, and reporting

This protocol is a two-arm superiority randomized controlled trial. It has been registered in Clinicaltrials.gov NCT05695599 and approved by the Ethics Committee of Clinical Research of Aragón (CEICA, Spain) with reference number C.I. PI22/380. In the event that changes to the protocol are necessary during its implementation, permission will be sought from the Ethics Committee before applying the changes. Participants will be randomly assigned to one of two groups: (1) the control group (CG) or (2) the WBV group. The study design and this protocol manuscript adhere to the SPIRIT reporting guidelines and the SPIRIT 2013 checklist is presented in Supplementary Table 1 [27]. Moreover, the exercise intervention is explained in accordance with the Consensus on Exercise Reporting Template (CERT): Explanation and Elaboration Statement [28]. The 16 items that should be completed in accordance with the CERT are presented in Supplementary Table 2.

As illustrated in Fig. 1, the study will span a period of 18 months. Four different assessments will be conducted at various intervals: T1 (approximately 1 week before the surgery), T2 (7 ± 1 weeks post-surgery), T3 (24 ± 2 weeks post-surgery), and T4 (18 months ± 2 weeks post-surgery).

**Fig. 1 Fig1:**
[figure not shown]
Study timeline

Due to the characteristics of the surgery and the expected recruitment difficulties, this study is expected to last a total of 4 years.

### Study setting

The study will be conducted at the public Clinico Lozano Blesa Hospital and the EXER-GENUD (EXERCISE-Growth, Exercise, Nutrition and Development) research group from the University of Zaragoza. Both locations are situated in Zaragoza, Spain.

### Participants

#### Sample size

The sample size for the present study was calculated using G*POWER 3.1. The F-test family, repeated measures, within-between interaction for two groups and four measurements was selected, assuming a correlation among the repeated measurements of 0.5. A total of 12 participants per group were required to achieve a power of 80% with a significance level of 5% under the assumption that we would find small-medium effect sizes (partial eta square of 0.06). This would entail a total of 24 participants. In the event of a 15% attrition rate during the experiment, it would be necessary to recruit an additional 3.6 participants. Consequently, the final study sample would be of 28 participants (14 per group).

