### Intervention

#### Randomization, allocation, and blinding

In order to ensure fairness, individuals who meet the eligibility criteria will be randomly assigned (1:1) to either a WBV group or a CG through the webpage https://www.sealedenvelope.com, taking sex into account (1:1). At the second visit, both groups will be provided with a brochure outlining the World Health Organization’s physical activity recommendations, as well as an ad hoc nutritional information sheet. A nurse will be responsible for recruiting all participants and will then direct them to the researchers, who will inform the participants of their group allocation, in accordance with the randomized order. Both groups will receive standard care, but the intervention group will also engage in an exercise intervention as outlined below. Given that the intervention will comprise WBV and that researchers will be involved in it, only the nurse and the statistician performing the statistics will be blinded. There is no foreseeable reason for the statistician to be unblinded to participant allocation.

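### The stated 80% power for a small-medium effect holds on neither reading of partial eta squared 0.06: N = 24 is powered for a difference of about 1 SD, or else has about 36–39% power

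*Protocol article*

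**What the plan says.** The Sample size section of the protocol article names G*Power 3.1 and the test: "The F-test family, repeated measures, within-between interaction for two groups and four measurements was selected". For the link between visits it adds one value for all outcomes: "assuming a correlation among the repeated measurements of 0.5". The result is 12 per arm for 80% power at the 5% level, and the effect behind that figure is described in these words: "under the assumption that we would find small-medium effect sizes (partial eta square of 0.06"). After an allowance for attrition, "the final study sample would be of 28 participants (14 per group"). The section does not say which of the program's effect-size specifications was used, cites no source for 0.06, and gives no difference or SD in outcome units.

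The Statistical methods section plans a repeated-measures ANOVA of the group-by-time interaction over the four assessments, so the powered test and the planned test are the same.

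**The concern.** A partial eta squared can be put on two scales in a repeated-measures power calculation. On one, the effect is standardised by the SD at a single visit, and the correlation and number of visits are then multiplied in. On the other, it is the partial eta squared that the repeated-measures ANOVA itself reports, computed against within-subject error, which already reflects the correlation. The same 0.06 means very different effects on the two scales, and the protocol does not say which it uses.

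At stake is what the trial can be said to detect. The text tells the reader that 12 per arm suffice for a modest effect. If that is not so, anyone judging the design, or later interpreting the interaction test, has the wrong figure for its sensitivity.

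**Working it through.** **Inputs (Sample size section).** k = 2 groups, m = 4 measurements, correlation ρ = 0.5, α = 5%, N = 24, partial η² = 0.06. Sphericity (ε = 1) is assumed, since no correction is stated there. Hence f² = 0.06/0.94 = 0.0638 and f = 0.253. Degrees of freedom at N = 24: (k−1)(m−1) = 3 and (N−k)(m−1) = 66. Power comes from the noncentral F distribution.

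**Step 1: reproduce the plan's figure.** With G*Power's default specification, λ = f²·N·m/(1−ρ) = 0.0638 × 24 × 4/0.5 = 12.26.

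| N | Power |
|---|---|
| 22 | 78.4% |
| 23 | 80.5% |
| 24 | 82.5% |

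The smallest even N reaching 80% is 24, as stated. Four other noncentrality formulas do not return 24:

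| λ | Smallest even N for 80% |
|---|---|
| f²·N·m | 46 |
| f²·N·(m−1) | 60 |
| f²·(N−k)(m−1) | 62 |
| f²·N | 174 |

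The default was therefore almost certainly used.

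**Step 2: what f = 0.253 means on that scale.** With two equal arms, f² is the variance over the four visits of the between-arm difference, in single-visit SD units, divided by 4. Assume the 16-week training falls between T2 (week 7) and T3 (week 24).

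- Equal at T1 and T2, apart by D at T3 and T4: variance D²/4, so f² = D²/16 and D = 4 × 0.253 = 1.01 SD.
- Apart at one visit only: variance 3D²/16, so f² = 3D²/64 and D = √(0.0638 × 64/3) = 1.17 SD.
- Growing linearly from T1 to T4: variance 5D²/36, so f² = 5D²/144 and D = √(0.0638 × 144/5) = 1.36 SD at T4.

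A simulation of 20,000 trials with 1.01 SD at T3 and T4 gave 82.7% power, which confirms the conversion.

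**Step 3: the same effect on the ANOVA scale.** Partial η² = λ/(λ + 66) = 12.26/78.26 = 0.157, or λ/(λ + 72) = 12.26/84.26 = 0.145 with N(m−1) in place of the error degrees of freedom. That is about 0.15.

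**Step 4: if 0.06 is the ANOVA's own partial η².**

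- λ = f²·(N−k)(m−1) = 0.0638 × 66 = 4.21 gives 35.6% power.
- λ = f²·N·(m−1) = 0.0638 × 72 = 4.60 gives 38.6% power.
- The corresponding difference at T3 and T4, from λ = (D²/16) × 24 × 4/0.5 = 12D², is D = √(4.21/12) = 0.59 SD. Simulation at that value gave 36.5% power.
- For 80% power, about 62 completers are needed with the first formula and about 60 with the second.

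**Step 5: detectable difference at N = 24.** Exactly 80% power needs λ = 11.57. With a difference D at T3 and T4, λ = 6D²/(1−ρ), so D = √(11.57(1−ρ)/6):

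| ρ | D for 80% power (SD) |
|---|---|
| 0.3 | 1.16 |
| 0.5 | 0.98 |
| 0.7 | 0.76 |
| 0.8 | 0.62 |
| 0.9 | 0.44 |

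At ρ = 0.5, a difference of 0.5 SD at T3 and T4 has 26% power and 0.8 SD has 61%. If sphericity fails, the 82.5% in step 1 falls to 73% at ε = 0.75 and 60% at ε = 0.5.

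**The case against.** The strongest reply is that nothing was miscalculated. The section gives the program, test and numerical inputs, and N = 24 follows from them under the default specification. This stands: the sample-size arithmetic is right for that specification.

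Several stronger readings are tempting, and the document does not support them.

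- A reader might infer that the correlation has been counted twice and that true power is simply 36%. That holds only if 0.06 was meant as, or taken from, the partial eta squared of a repeated-measures ANOVA. The section gives no source for 0.06; if it is a benchmark placed on the default scale, the correlation enters once, as that scale requires.
- A reader might infer that 0.06 means about 1 SD whatever the convention. It does not: on the ANOVA scale it is about 0.6 SD.
- A reader might infer that the trial can detect only very large differences. That rests on ρ = 0.5. The protocol applies this one value to all outcomes, and an outcome with correlation 0.9 would need only 0.44 SD.
- A reader might infer that a null result will be taken as proof of no effect. No section says so.
- A reader might object that 28 recruits less 15% leave 28 × 0.85 = 23.8. This is immaterial: 23 completers still have 80.5% power on the plan's own calculation.

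What the reply does not rescue is the pairing of 80% power with a small-medium effect. On the default scale, at the protocol's own correlation, the effect is about 1 SD; on the ANOVA scale, the power is not 80%.

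**Conclusion.** The point holds as a fault of effect-size scale and label. On the default scale, 24 completers have 82.5% power for 1.01 SD at T3 and T4 (1.17 SD if at one visit only), an ANOVA partial eta squared of about 0.15. On the scale of the planned ANOVA, 0.06 has about 36–39% power and would need about 60–62 completers. No reading of the stated inputs yields 80% power for a small-medium effect with 24.

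The SD figures assume equal arms, ρ = 0.5, sphericity, and training between T2 and T3. That the default specification was used is an inference from the fact that it alone, of the five formulas tried, returns 24.

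**What to change.** Keep 28 participants and the planned test, and restate the Sample size paragraph so that it:

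1. names the G*Power effect-size specification used;
2. says that 24 completers give 80% power for a between-arm difference of about 1.0 SD at both T3 and T4, at correlation 0.5 and under sphericity, equal to an ANOVA partial eta squared of about 0.15;
3. gives the range over the correlation: about 1.16 SD at 0.3, 0.76 SD at 0.7 and 0.44 SD at 0.9;
4. says that power at an ANOVA partial eta squared of 0.06 is about 36–39%;
5. deletes the small-medium label.

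The change needs no extra participants and no change of design. Its cost is that the stated sensitivity becomes less favourable.

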#### Eligibility criteria

Inclusion criteriaIndividuals undergoing a SG with a BMI above 40 kg/m^2^ and a body mass of less than 180 kgAged between 18 and 50 years

Exclusion criteriaHave suffered any type of cancer in the last 5 yearsHave a pacemaker or have been diagnosed with a cardiac problem that disables the patient from participating in an exercise programHave suffered an acute myocardial infarction in the last 6 monthsHave recently suffered a fractureHave any other condition that the physician deems as a contraindication for performing supervised physical exercise

#### Recruitment

The recruitment process will be conducted in the Clinico Lozano Blesa Hospital, where each selected participant will engage in an individualized meeting with a nurse. Should they meet the inclusion criteria and decide to participate, they will be required to sign an informed consent. Furthermore, the informed consent form will also require the participants to consent to the collection of biological specimens (stools and blood samples).

### Intervention

#### Randomization, allocation, and blinding

In order to ensure fairness, individuals who meet the eligibility criteria will be randomly assigned (1:1) to either a WBV group or a CG through the webpage https://www.sealedenvelope.com, taking sex into account (1:1). At the second visit, both groups will be provided with a brochure outlining the World Health Organization’s physical activity recommendations, as well as an ad hoc nutritional information sheet. A nurse will be responsible for recruiting all participants and will then direct them to the researchers, who will inform the participants of their group allocation, in accordance with the randomized order. Both groups will receive standard care, but the intervention group will also engage in an exercise intervention as outlined below. Given that the intervention will comprise WBV and that researchers will be involved in it, only the nurse and the statistician performing the statistics will be blinded. There is no foreseeable reason for the statistician to be unblinded to participant allocation.

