### Statistical methods

The Shapiro–Wilk test will be used to test for normality of the data while variance homogeneity and sphericity will be assessed with the Levene and Mauchly tests, respectively. To assess changes over time in the assessed outcomes, a repeated-measures ANOVA with Bonferroni correction will be used to assess the interaction between group (control group vs. WBV) and time (baseline vs. 2nd vs. 3rd vs. 4th assessments). In the absence of a normal distribution, data will be analyzed with the Wilcoxon test for within-group comparisons and the Mann–Whitney test for between-group comparisons using Bonferroni’s correction. To test for associations between variables, both correlations and linear regressions will be performed. The significance level will be set at 5%. Per-protocol and intention-to-treat analyses will be performed in order to account for the possible dropouts during the study. In the per-protocol analysis, we will include only the participants who attend at least 70% of the sessions and undergo the baseline and post-intervention outcome assessments. For the intention-to-treat analysis, we will consider all the participants who will undergo the baseline assessments and subsequently participate in at least one additional assessment following their group assignment will be considered.

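### Sex enters the allocation but not the stated analysis: adding sex and sex-by-time is nearly free and protects power if change after surgery differs by sex

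*Protocol article*

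**What the plan says.** Under Randomization, allocation, and blinding, eligible people "will be randomly assigned (1:1) to either a WBV group or a CG", "taking sex into account (1:1"). The Methods part of the abstract plans "Twenty-eight participants (14 females), aged 18 to 50 years". The protocol does not say whether sex enters through strata, blocks or another device. In a sentence about random assignment, the natural reading is that sex is balanced between the arms, which would put about 14/2 = 7 women and 7 men in each.

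Under Statistical methods, the test is a repeated-measures ANOVA "to assess the interaction between group (control group vs. WBV) and time (baseline vs. 2nd vs. 3rd vs. 4th assessments"). For data that are not normal, the arms are compared by "the Mann–Whitney test for between-group comparisons using Bonferroni’s correction". Sex appears in neither.

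The sample size rests on the same two-factor test: "within-between interaction for two groups and four measurements was selected", "assuming a correlation among the repeated measurements of 0.5".

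**The concern.** Balancing the arms on a factor takes its variation out of the arm contrast. An analysis that omits the factor leaves that variation in the error term. The standard error is then too large for the contrast, the test rejects too seldom under the null, and the precision that balancing bought is not used.

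This trial has little power to spare: 12 completers per arm are planned for 80% power. The primary outcomes include body composition, the Bruce test and basal metabolic rate, on which women and men plausibly differ. The question is whether such a difference reaches the test that the protocol plans, and by how much.

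**Working it through.** **Inputs from the protocol (Sample size).** Partial eta squared 0.06, two groups, m = 4 measurements, correlation 0.5, alpha 5%, N = 24 (12 per group), 28 recruited.

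**Assumed.** The documents give no sex effect. Ranges used: a difference in level of 0 to 2 SD, and a sex-by-time difference that grows linearly from 0 at the first visit to 0.5, 1 or 2 SD at the fourth. Sex is taken as balanced between arms, and the covariance as compound symmetric.

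**Step 1: the protocol's own figure.**
- f² = 0.06/0.94 = 0.0638, so f = 0.2526.
- Noncentrality = f² × N × m/(1 − correlation) = 0.0638 × 24 × 4/0.5 = 12.26.
- Degrees of freedom: 3 and 3 × (24 − 2) = 66.
- Power = 82.5%. At N = 23 it is 80.5%, so 24 is the smallest balanced number that reaches 80%. The stated figure is reproduced.

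**Step 2: a constant sex difference.** The interaction test uses only deviations from each participant's own mean, so a constant difference drops out. In simulation (20,000 trials per setting, N = 24), a level difference of 1 or 2 SD gave type I error of 4.9 to 5.0% and power of 82 to 83%, with or without sex.

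**Step 3: a sex-by-time difference.** This does not drop out.
- The visit pattern 0, 1/3, 2/3, 1 has a sum of squares about its mean of 2 × (1/2)² + 2 × (1/6)² = 0.556.
- With half of each sex, a difference of d SD adds (24/4) × d² × 0.556 = 3.33d² to an error sum of squares expected to be 66 × 0.5 = 33.
- The error mean square is therefore inflated by 3.33d²/33: 2.5% at d = 0.5, 10% at d = 1 and 40% at d = 2.

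Simulation of the planned F test at N = 24 gave:

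| Sex-by-time difference at last visit | Type I error, without sex | Type I error, with sex | Power, without sex | Power, with sex |
|---|---|---|---|---|
| 0.5 SD | 4.7% | 5.1% | 81–82% | 82–83% |
| 1 SD | 3.4–3.5% | 4.9% | 78–79% | 82–83% |
| 2 SD | 1.3% | 5.0% | 65% | 82–83% |

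Ranges span two independent simulations. At N = 28, power is 85.4% against 88.5% at 1 SD, and 75.2% against 88.5% at 2 SD.

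**Step 4: the fallback.** If it compares raw values at one visit, a difference in level matters too. Using a t test as a stand-in at N = 24, a 1 SD level difference gave type I error of 2.8% against 5.0% with sex in the model, and power of 15% against 22%. Rank tests were then run directly with 6 per sex and arm, a group difference of 1 SD and sex explaining an assumed 20% of variance. Plain Mann–Whitney had type I error of about 2.1% and power of 60%; the sex-stratified van Elteren test had about 4.2% and 69%.

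**Step 5: the price if sex has no effect.** In the F test, the error degrees of freedom fall from 66 to 3 × (24 − 3) = 63, and power from 82.46% to 82.34%. In the rank test, power falls from 59.9% to 58.4%.

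**The case against.** **The main test may lose nothing.** This stands in part. That women and men differ on the primary outcomes is mainly an argument about level, and level cancels from the group-by-time test. Nothing in the protocol shows that change after surgery differs by sex. A reader might infer that the planned tests are conservative and underpowered as they stand; the documents do not support that.

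**A simple change-score analysis suggests a larger loss.** With sex explaining 20% of the variance of one change score, a t test has about 65% power without sex and 74% with it. A reader might take those 9 points as the loss here. But that is not the planned test: at a roughly comparable sex effect (1 SD), the four-visit F test loses about 4 points.

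**The allocation wording is loose.** It could mean only that equal numbers of each sex are recruited. The conservatism argument needs balance between arms. That is the natural reading, but it is not confirmed.

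**The fallback may be run on changes.** The protocol does not say. On changes, a constant sex difference cancels there as well, and only a sex-by-time difference would matter.

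**Covariates belong in the statistical analysis plan.** This is usually fair, and more so for a condensed article. Here, though, the article names the test and its factors and sizes the trial on the same two factors. The point is a specific change to a stated method. It does not rest on a missing detail.

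**Conclusion.** The mismatch holds: sex is used in allocation and is in neither stated analysis. Its effect is conditional. A constant sex difference does no harm to the group-by-time test. A sex-by-time difference makes that test conservative and costs about 1 point of power at 0.5 SD, 4 at 1 SD and 17 to 18 at 2 SD, at N = 24. The fallback is exposed to a difference in level as well, if it compares values at a visit.

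These sizes rest on sex being balanced between arms, a linear divergence over the visits and the protocol's correlation of 0.5. The sex effects themselves are assumptions. False-positive control is not at risk, because the error runs only in the conservative direction. This is a free or cheap improvement, held with moderate confidence; it does not threaten the trial's validity.

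**What to change.** In the Statistical methods section, add sex and sex-by-time as fixed terms to the repeated-measures model, keeping group-by-time as the test of interest. Replace the plain Mann–Whitney comparison with a sex-stratified (van Elteren) rank test, and say whether it is applied to values at a visit or to changes from baseline. In the allocation section, state how sex is used in the randomisation. Make the change before any outcome is compared by group, so that adjustment is not a choice made after seeing results.

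Cost: a line or two of wording and no new data, since sex is already recorded. The model spends one between-person and three within-person degrees of freedom. If sex turns out not to matter, the loss is about 0.1 point of power in the F test and 1 to 2 points in the rank test.
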